**Sponsor: Chongqing University Cancer Hospital**

## **1. Background of the research**

As a routine clinical operation, central venipuncture has played a great role in clinical treatment. It includes emergency rapid blood transfusion, infusion, invasive hemodynamic monitoring, infusion of vasoactive drugs, chemotherapy drugs, parenteral nutrition drugs and hemodialysis. The internal jugular vein (IJV) is one of the most common options for establishing central venous access. With the rapid development of economy in our country and the change of modern lifestyle and dietary structure, the adult obesity in our country is as high as 160 million, the obesity rate about 11.9%. The traditional anatomic marker location IJV puncture catheterization often leads to the difficulty of puncture catheterization in obese patients, and is prone to various mechanical complications, such as misplaced artery puncture, hematoma, pneumothorax, etc. Ultrasound-guided internal jugular vein catheterization can significantly reduce the risk of puncture-related complications and improve the success rate of one-time puncture.

At present, clinical studies mainly focus on the comparison of short-axis method, long-axis method, oblique axis method and the improved methods of the above methods, in order to find the safest and most efficient ultrasound-guided IJV puncture catheter method. A large number of studies have shown that the oblique axis method and the improved combined method show advantages. By comparing oblique axis method and modified combined short and long axis method, this study intends to study the differences in ultrasonic anatomy of obese patients under oblique axis and short-axis method, and compare the differences in puncture time, puncture success rate and puncture complications between the combined method and the oblique axis method, so as to find the ultrasound-guided IJV puncture method that is most suitable for obese patients, and promote the technology to improve the regional medical technology level. It is of great clinical significance.

## **2. Objective of the study**

To evaluate the safety and effectiveness of modified combined short and long axis technique in right internal jugular vein puncture, compare the difference between it and oblique axis method in puncture success rate and puncture complications, find the most suitable method for right internal jugular vein puncture in obese patients, and promote the technology to improve the regional medical technology level.

## **3. Research Scheme**

## **1) Research design**

This is a single-center, randomized, controlled, non-inferiority, evaluator blind clinical study. The modified combined short and long axis method will be selected as the experimental group and the inclined axis method as the control group, and 190 subjects will be planned to be included in the study according to 1:1 balanced allocation.

## **2) Inclusion criteria**

- (1) The subjects voluntarily join the study, sign the informed consent, and the compliance is good;
- (2) Age: 18-75 years old (when the informed consent is signed);
- (3) Patients who be admitted to our hospital for elective surgery and plan to undergo right internal jugular vein puncture catheterization.

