## **3) Exclusion criteria**

- (1) Abnormal coagulation function; (2) infection of the puncture site; (3) ASA grade >III; (4) neck scar; (5) patients with a history of neck trauma or surgery; (6) History of right internal jugular vein catheterization within 1 month; (7) Patients with blood system diseases; (8) patients with mental diseases; (9) anatomic variation, no right IJV; (10) IJV plaque thrombosis; (11) the ultrasound imaging was not clear.

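### The objective asks which method suits obese patients best, but no eligibility criterion requires obesity, so the sample as written cannot support that clause of the objective

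*Protocol*

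**What the plan says.** **Target population.** Protocol section 1 (Background of the research) presents difficult landmark-guided puncture in obese patients as the problem. It says the two methods are to be compared "so as to find the ultrasound-guided IJV puncture method that is most suitable for obese patients". Section 2 (Objective of the study) repeats this as an aim: "find the most suitable method for right internal jugular vein puncture in obese patients". The same section also aims to evaluate the safety and effectiveness of the modified combined method and to compare success and complications with the oblique axis method. Those clauses are not worded as limited to obese patients.

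**Eligible population.** Section 2) Inclusion criteria has three numbered items:
- "The subjects voluntarily join the study, sign the informed consent, and the compliance is good"
- an age range of 18 to 75 years
- "Patients who be admitted to our hospital for elective surgery and plan to undergo right internal jugular vein puncture catheterization"

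Section 3) Exclusion criteria has eleven items, ending with "9) anatomic variation, no right IJV; (10) IJV plaque thrombosis; (11) the ultrasound imaging was not clear". None refers to weight or BMI.

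**Elsewhere.** Section 4) Grouping and randomization describes blocks of 4 at 1:1 and names no stratification factor. Sections 7) and 8) name no obese subgroup, and the general mention of adjustment for confounders in 8.2 does not name BMI. The protocol nowhere defines obesity. Section 8.1 assumes success rates of 95% and 90% without saying whose rates they are.

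**The concern.** The population named in the purpose of the trial and the population admitted by its criteria are different. Eligibility is core protocol content: the anaesthesiologist enrols on these criteria at the preoperative visit. A later analysis plan could define an obese subgroup, but it could not supply obese patients who were never recruited.

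A statement about the best method for obese patients would then rest either on extrapolation from a general elective-surgery sample or on whatever obese patients happened to be enrolled. The planned 90% power applies to obese patients only if everyone enrolled is obese.

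**Working it through.** **1. Does any provision restrict the sample to obese patients?**

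| Provision | Obesity or BMI condition |
|---|---|
| Background, Objective | obese patients named as the target |
| Inclusion criteria (3 items) | none |
| Exclusion criteria (11 items) | none |
| Randomization | no stratification stated |
| Outcomes and statistical analysis | no obese subgroup stated |
| Sample size assumptions | population not stated |

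The inclusion list is numbered and complete, so the gap does not come from missing text.

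**2. Reproduce the plan's sample size.** Inputs from section 8.1: 95% (modified combined method), 90% (oblique axis method), margin −8 points, level 0.025 (taken as one-sided), power 90%, dropout 10%.

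- Variance term: 0.95 × 0.05 + 0.90 × 0.10 = 0.0475 + 0.0900 = 0.1375.
- Distance from the assumed difference to the margin: 0.05 + 0.08 = 0.13.
- n per arm = (1.960 + 1.282)² × 0.1375 / 0.13² ≈ 85.5, rounded up to 86. The plan states 85.
- Power at 85 per arm: 89.8%.
- Dropout: 85 / 0.90 = 94.4, rounded up to 95 per arm.

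The plan's figure reproduces to within one patient, so the arithmetic is not the problem. What is open is the population to which the figure applies.

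**3. Illustration: the obese part of an unrestricted sample.** The Background gives the national adult figure: "the adult obesity in our country is as high as 160 million, the obesity rate about 11.9" percent. The obese share among this hospital's eligible patients is not given, so applying 11.9% to the trial is an assumption.

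- Expected obese patients: 190 × 0.119 = 22.6, or 11.3 per arm before dropout.
- After dropout (85 per arm): 170 × 0.119 = 20.2, or 10.1 per arm.
- Half-width of the 95% interval = 1.96 × √(0.1375 / n).
  - n = 11.3: 21.6 points.
  - n = 10.1: 22.9 points.
  - n = 85: 7.9 points, close to the 8-point margin.
- Power = Φ(0.13 / √(0.1375 / n) − 1.96).
  - n = 11.3: 22%.
  - n = 10.1: 20%.

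The same formulas at other assumed shares:

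| Assumed obese share | Obese per arm, before dropout | Half-width, before dropout | Power before / after dropout |
|---|---|---|---|
| 5% | 4.75 | 33 points | not calculated |
| 11.9% | 11.3 | 22 points | 22% / 20% |
| 20% | 19 | 17 points | 33% / 30% |
| 30% | 28.5 | 14 points | 46% / 42% |
| 50% | 47.5 | 11 points | 68% / 63% |

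All of these use a normal approximation. At 11.3 per arm the expected failures are 11.3 × 0.05 ≈ 0.6 and 11.3 × 0.10 ≈ 1.1, so the approximation is rough there and rougher still at the 5% share. The values show order of magnitude only.

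**The case against.** **The general comparison survives.** A reader might infer that the trial cannot answer its question at all. The documents do not support that. Evaluating the modified method and comparing it with the oblique axis method are aims without an obesity restriction, and a general sample can address them. Only the obese-patient clause is left without support. This objection stands and limits the point.

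**The investigators may intend to enrol only obese patients.** This is possible, and the stated purpose suggests it. But enrolment follows the written criteria, and intent alone gives neither a cut-off nor a screening rule.

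**The subgroup figures are hypothetical.** This also stands. The 11.9% is a national adult rate, the protocol plans no obese subgroup analysis, and the approximation is weak at about 11 per arm. The contradiction between objective and criteria does not depend on these figures.

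**Would non-obese patients make non-inferiority easier to show?** A reader might infer that easier necks raise success in both arms, shrink the difference and so favour non-inferiority. The protocol's own assumptions do not support this. Section 8.1 assumes the modified method is 5 points better, so a smaller difference brings the expected result closer to the margin. At 85 per arm, with 95% in both arms, the standard error is √(2 × 0.0475 / 85) = 0.0334, and power is Φ(0.08 / 0.0334 − 1.96) ≈ 67%, down from about 90%. Power is about 76% at 96% in both arms and 86% at 97%. It exceeds the plan only near the ceiling (96% at 98% in both arms) or where part of the advantage remains (91% at 97% against 95%). The direction is therefore undetermined. The premise is also undocumented: the Background links difficulty in obese patients to the landmark technique and gives no ultrasound-guided success rates by body weight.

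**Conclusion.** Wrong as written. The Background and Objective target obese patients, while the eligibility criteria admit adults aged 18 to 75 of any weight, and nothing else in the protocol closes the gap. The sample so defined cannot support a conclusion about the most suitable method in obese patients. This rests on the text alone and needs no assumption.

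The size of the shortfall does need one. If the obese share were 11.9%, about 23 of 190 patients would be obese, with a half-width of about 22 points and power of about 20–22% under the stated 95% and 90% rates. Over assumed shares of 5% to 30% the half-width runs from about 33 to 14 points, and even a 50% share leaves power at about 68%.

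No bias toward non-inferiority is claimed, and the general comparison of the two methods is unaffected.

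**What to change.** Reconcile the Background and Objective with the eligibility criteria in one of two ways.

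1. **Keep the obese-patient aim.** Add an inclusion criterion with the sponsor's own definition of obesity, with BMI measured at the preoperative visit and recorded in the case report form. The protocol mentions an anaesthesia assessment at that visit but does not say that BMI is taken, so the measurement should be written in. If the 95% and 90% rates were meant for obese patients, the sample size stays at 95 per arm. The cost is an amendment and possibly slower recruitment than the 12 months planned in section 11) Research progress.

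2. **Keep the open criteria.** Remove the obese-patient claim from the Background, the Objective and the conclusions. The cost is that the result is no longer specific to obese patients.

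Under either option, state in section 8.1 which population the 95% and 90% rates describe. If it is not the population enrolled, the sample size has to be recalculated.

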## **3) Exclusion criteria**

- (1) Abnormal coagulation function; (2) infection of the puncture site; (3) ASA grade >III; (4) neck scar; (5) patients with a history of neck trauma or surgery; (6) History of right internal jugular vein catheterization within 1 month; (7) Patients with blood system diseases; (8) patients with mental diseases; (9) anatomic variation, no right IJV; (10) IJV plaque thrombosis; (11) the ultrasound imaging was not clear.

## **4) Grouping and randomization**

Generating a random number table using a computer. On the day before surgery, during the preoperative visit, the attending anesthesiologist involves in the anesthesia assessment, will base on inclusion and exclusion criteria, signe the informed consent for the clinical study with the patients. According to a block size of 4, the enrolled patients will be randomized in a 1:1 ratio into two groups: the M group, consisting of 95 patients, receiving the modified combined short and long axis method , and the O group, consisting of 95 patients, receiving the oblique-axis method.

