## **5) Blind method**

In order to enhance the reliability of the results of this study and the conclusions derived

therefrom, on the basis of a comprehensive evaluation of the feasibility of the study, the random number table is sealed in a non-transparent envelope and will be kept by specially trained full-time personnel who are not involved in this experiment. Due to the characteristics of the operation itself, the operator could not implement the blind method. In this study, the patients and the personnel involve in data recording and collating will be blinded.

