### **6.2.2 Puncture and image acquisition protocol**

All right internal jugular vein puncture catheterization procedures will be performed by the same senior attending physician who is proficient in both methods. A one-man technique will be used (the same operator operated the ultrasound probe and puncture needle) using the 12L5-A high frequency probe of the Mindray M9T notebook color ultrasound diagnostic system with a probe length of 4.7cm (set frequency 7.5-10 MHz and depth of 5cm). After the patient be anesthetized, the pillow will be removed and the patient lay flat with the head tilted 30 degree to the left and the head low and the foot high at 15 degree. Before preparing for skin disinfection, preoperative ultrasound examination will be performed to identify IJV and CCA in the images (generally IJV is shallower than CCA, the vessel wall is thin, the diameter is thick, the lumen is oval, the size can change with breathing, and the probe can be pressed flat; CCA position is deep, the blood vessel wall is thick, the diameter is thin, the lumen is round, and the probe pressure can not squish it. Color Doppler ultrasound imaging technology will be used, and the probe will be oriented towards the proximal end. It could be seen that the red blood flow signal area is CCA, while the blue blood flow signal area is IJV), patency of the internal jugular vein. The adjacent relationship between IJV and CCA in the short axis plane and oblique axis plane of all patients will be observed at the thyroid cartilage level, and ultrasound images will be collected and saved.

After the images be saved, the modified combined short and long axis method and oblique axis method will be performed according to the group conditions. First, routine disinfection will be performed, sterile tissue will be laid, the ultrasonic probe will be put into the sterile protective cover, and 10 ml of sterile ultrasonic coupling agent will be injected into the protective cover, and the probe cover will be fixed. In the modified combined short and

long axis method, ultrasonic probe will be fixed the radiopaque barium line at the center line of the probe in advance. The two groups of operation methods are as follows:

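### A single block size of 4, written into the protocol of a single-centre, one-operator open trial, leaves allocations open to prediction

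*Protocol*

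**What the plan says.** - Protocol, 4) Grouping and randomization: "According to a block size of 4, the enrolled patients will be randomized in a 1:1 ratio into two groups". The same section sets each arm at exactly 95: "the M group, consisting of 95 patients" and "the O group, consisting of 95 patients, receiving the oblique-axis method". It gives eligibility assessment and consent to the attending anesthesiologist, at a visit on the day before surgery.
- Protocol, 1) Research design: the trial is single-centre, and "190 subjects will be planned to be included in the study according to 1:1 balanced allocation".
- Protocol, 6.2.2: "All right internal jugular vein puncture catheterization procedures will be performed by the same senior attending physician".
- Protocol, 5) Blind method: "the operator could not implement the blind method". The random list is kept in an opaque envelope by trained staff outside the trial; patients and data recorders are blinded.

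The protocol does not mention a second block size, stratification, or withholding of the block size from operator or enrolling staff. It also does not say when or how each assignment is released.

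**The concern.** A permuted block must end in balance, so later places in a block can be deduced from earlier ones. The deduction needs three things: the block size, a record of past allocations, and knowledge of where each block starts. Here the block size is printed in the protocol. With one centre and no stratification mentioned, there appears to be a single sequence. One unblinded person carries out every allocated procedure and so could follow that sequence from the start. An opaque envelope hides the list but not this inference.

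The stake is selection bias. If someone who influences entry to the trial can foresee the arm, a difficult patient can be deferred or screened out according to the next assignment. The primary outcome is sensitive to small numbers. At the assumed success rates of 95% and 90%, about 0.05 × 95 = 4.75 and 0.10 × 95 = 9.5 failures are expected. One patient moves an arm's rate by 1/95 = 1.05 points. As an illustration only, four likely failures replaced by successes in one arm would move the difference by 4/95 = 4.2 points, about half the 8-point non-inferiority margin.

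**Working it through.** **Inputs.** Block size 4 and 1:1 allocation (4) Grouping and randomization); total 190 and one centre (1) Research design); one operator (6.2.2), unblinded (5) Blind method); assumed rates 95% and 90%, margin 8 points, level 0.025 and 10% dropout (8.1 Sample estimation).

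**The plan's own figure.** Taking 0.025 as one-sided, with an unpooled normal approximation:

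n = (0.95 × 0.05 + 0.90 × 0.10) × (1.960 + 1.282)² / (0.05 + 0.08)² = 85.5 per arm.

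The stated 85 gives 89.8% power, and 85/0.9 = 94.4, hence 95 per arm and 190 in total. The sample size reproduces and is not in dispute.

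**Predictability with a fixed block of 4.** There are 6 equally likely orders of two M and two O. The observer knows the size and all past allocations, guesses the arm with more places left, and tosses a coin when the two are equal.

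| Place in block | Chance that it is certain | Chance that the best guess is right |
|---|---|---|
| 1 | 0 | 1/2 |
| 2 | 0 | 2/3 |
| 3 | 1/3 (first two places the same arm: 2 of 6 orders) | 1/3 × 1 + 2/3 × 1/2 = 2/3 |
| 4 | 1 | 1 |
| Sum | 1.333 | 2.833 |
| Per allocation | 1.333/4 = 33.3% | 2.833/4 = 70.8% |

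Over 190 patients there are 47 full blocks and 2 further places. Expected certain allocations: 47 × 1.333 + 0 = 62.7, or 62.7/190 = 33.0%. Expected correct guesses: 47 × 2.833 + 1/2 + 2/3 = 134.3, or 70.7%. An unpredictable list would give 95.

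**Predictability with varied blocks.** Simulation of 1,000 lists of 190, block sizes drawn with equal probability, for an observer who knows the possible sizes and all past allocations but not the size of each block:

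| Scheme | Certain | Best guess right |
|---|---|---|
| Fixed 4 (check against the exact result) | 32.9% | 70.7% |
| 4 or 6 | 5.4% | 69.3% |
| 4, 6 or 8 | 2.4% | 68.0% |

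With sizes 4, 6 and 8, certain allocations fall from about 63 to about 0.024 × 190 = 4.6. Correct guesses fall only from about 134 to about 0.680 × 190 = 129, so the excess over chance falls from about 39 to about 34. Varying the sizes removes nearly all certainty but little of the guessing advantage. That advantage depends on seeing past allocations and knowing the scheme.

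**The 95/95 wording.** 190/4 = 47.5, so the last block is half used if recruitment stops at exactly 190 and every block has size 4. The first two places of a block differ in 4 of 6 orders, so P(95/95) = 2/3 and P(96/94 or 94/96) = 1/3. With all 190 evaluable, power is 92.7% at 95/95, 92.8% with 94 in M and 96 in O, and 92.7% with 96 in M and 94 in O. The change is below 0.1 point.

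**The case against.** The strongest reply is that the step from a predictable list to biased enrolment is not documented. Eligibility and consent belong to the attending anesthesiologist at the preoperative visit, and punctures to one senior physician. Nothing says that these are the same person or that the anesthesiologist sees earlier allocations, and custody of the list is independent. This stands: the 33% and 71% are ceilings for an observer who knows the block size, follows every allocation and knows where blocks start. What remains is that the protocol does not keep the two roles apart and does not withhold the block size from either.

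A reader might also infer that the block size lets the operator use the exclusion for poor ultrasound image quality selectively by arm. The documents do not support that link. The only ultrasound examination described comes just before skin disinfection, after the enrolment visit, and the time at which the assignment is revealed is not given. If it is revealed before the scan, the arm is known under any block scheme; the problem would then be exclusion after randomization, which varied blocks would not cure.

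Two further replies have force. Varied blocks lower the best-guess rate only slightly, so the gain must not be oversold. And the 190 and 95 can be read as targets: a final block of 2, which the protocol does not rule out, would give 95/95. On that reading the unequal split is at most a point of wording.

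**Conclusion.** The concern holds as a potential weakness in allocation concealment. The protocol fixes and discloses one block size of 4 where a single unblinded operator could follow the whole sequence. For someone who does so, about 33% of allocations are certain and about 71% can be guessed. This assumes one unstratified list used in order, and knowledge of the block size and of every past allocation.

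A reader might go further and conclude that concealment has been broken, or that the operator selects patients by arm. The documents support neither, since they do not say who, if anyone, both enrols and sees past allocations. The possible 96/94 split is a minor remark with negligible effect on power. The protocol should still be changed, because a better scheme is available at little cost.

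**What to change.** 1. Generate the list with randomly varying block sizes, for example 4, 6 and 8.
2. Keep the sizes with the independent custodian, and state in the protocol seen by the operator and enrolling staff only that randomization is in blocks of undisclosed, varying size. This matters at least as much as the first step.
3. Release one assignment at a time, only after eligibility is confirmed and the patient is enrolled, and say in the protocol when this happens.
4. State whether the operator may enrol patients and whether the enrolling anesthesiologist can see earlier allocations.
5. As a wording change, write about 95 per group.

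Cost: the list must be regenerated and the protocol text amended; section 9) requires written ethics approval of the protocol. The planned sample size and power are essentially unaffected. If recruitment has started, the change protects only the remaining allocations.
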